## Abstract

**Background:**

Insertion of a ventriculoperitoneal shunt (VPS) for the treatment of hydrocephalus is one of the most common neurosurgical procedures in the UK, but failures caused by infection occur in approximately 8% of primary cases. VPS infection is associated with considerable morbidity and mortality and its management results in substantial cost to the health service. Antibiotic-impregnated (rifampicin and clindamycin) and silver-impregnated VPS have been developed to reduce infection rates. Whilst there is some evidence showing that such devices may lead to a reduction in VPS infection, there are no randomised controlled trials (RCTs) to support their routine use.

**Methods/design:**

Overall, 1,200 patients will be recruited from 17 regional neurosurgical units in the UK and Ireland. Patients of any age undergoing insertion of their first VPS are eligible. Patients with previous indwelling VPS, active and on-going cerebrospinal fluid (CSF) or peritoneal infection, multiloculated hydrocephalus requiring multiple VPS or neuroendoscopy, and ventriculoatrial or ventriculopleural shunt planned will be excluded. Patients will be randomised 1:1:1 to either standard silicone (comparator), antibiotic-impregnated, or silver-impregnated VPS. The primary outcome measure is time to VPS infection. Secondary outcome measures include time to VPS failure of any cause, reason for VPS failure (infection, mechanical failure, or patient failure), types of bacterial VPS infection (organism type and antibiotic resistance), and incremental cost per VPS failure averted.

**Discussion:**

The British antibiotic and silver-impregnated catheters for ventriculoperitoneal shunts multi-centre randomised controlled trial (the BASICS trial) is the first multi-centre RCT designed to determine whether antibiotic or silver-impregnated VPS reduce early shunt infection compared to standard silicone VPS. The results of this study will be used to inform current neurosurgical practice and may potentially benefit patients undergoing shunt surgery in the future.

**Trial registration:**

International Standard Randomised Controlled Trial Number:
ISRCTN49474281.

## Background

Hydrocephalus affects one in every 500 births, and is thus one of the most common causes of developmental disabilities in children. The condition also affects older children and adults of all ages and can be secondary to a variety of causes including intracranial tumours, haemorrhage, and infection. In the late 1950s, the development of treatment with cerebral shunts revolutionised the management of these patients. Standard treatment for hydrocephalus remains the ventriculoperitoneal shunt (VPS), which is composed of silicone tubing and a valve and which drains cerebrospinal fluid (CSF) from the ventricles into the peritoneal cavity. Insertion of a VPS for hydrocephalus is now one of the most common procedures performed in neurosurgical units, and between 3,000 and 3,500 shunt operations are carried out in adults and children per year in the UK
[1]. Shunt failure due to infection has plagued this neurosurgical advance ever since it was developed. The incidence of shunt infection varies markedly in the literature from 3 to 27%
[2-6] and is higher in certain groups, for example neonates, children under 1 year old, and patients treated with a previous temporary external ventricular drain (EVD). Episodes of shunt infection have a significant impact on patients, in terms of health-related quality of life, cognitive function and IQ
[7], and survival, with the number of shunt infections being an independent predictor of death in patients requiring CSF shunts (HR 1.66, 95% CI: 1.02 to 2.72)
[8]. Impacts on health services are also significant; these include the requirement for prolonged inpatient hospitalisation, additional surgery to remove the infected hardware, placement of a temporary EVD (a temporary tube placed in the ventricles that are prone to infection), intravenous and intrathecal antibiotics, and further surgery to place a new shunt once the infection has been treated.

Currently there are three types of shunt catheter available: standard, antibiotic-impregnated, and silver-impregnated. There is no evidence on their comparative effectiveness, and consequently practice is variable across the UK and worldwide, with selection being according to surgeon preference. The three main types of VPS catheters on the market are:

1. Standard VPS made of silicone.

2. Antibiotic-impregnated VPS made of silicone and impregnated with antibiotics (0.15% clindamycin and 0.054% rifampicin). This type has been on the market for approximately 9 years and has been adopted by the neurosurgical community as a means to potentially reduce shunt infection, despite the fact that it is more expensive and evidence is lacking. A recently published systematic review and meta-analysis of antibiotic-impregnated VPS identified one randomised controlled trial (RCT) and 11 observational studies. The RCT, conducted in a single centre in South Africa, demonstrated a trend favouring the antibiotic-impregnated VPS compared to standard VPS, but did not show a statistically significant difference between the two groups in the risk of shunt infection (RR: 0.38, CI: 0.11, 1.30; *P* = 0.12); however, a meta-analysis of the 11 observational studies showed a statistically significant difference favouring the antibiotic-impregnated VPS (RR: 0.37, CI: 0.23,0.60; *P* <0.0001)
[9]. Research on antibiotic-impregnated VPS in Liverpool has shown that over a 2-year period the infection rate was reduced in paediatric patients compared to historical controls
[10]. However continued data collection over 3.5 years and published as part of a Liverpool-led multi-centre observational study with two other UK paediatric neurosurgical units showed no significant reduction in infection in Liverpool
[11]. Indeed the reduction in infection achieved by antibiotic-impregnated VPS in the multi-centre observational study was only seen in neonates and was heavily weighted by the results from one unit. This latter study
[11] was not part of the published systematic review
[9].

3. Silver-impregnated VPS made of silicone and impregnated with silver. This type was launched in the UK in March 2011 with similar infection claims. There is little doubt that silver ions have antimicrobial effects and they elute from silver-impregnated catheters. However the efficacy of silver-impregnated catheters at preventing VPS infections is not yet proven. There is one observational study of silver-impregnated VPS used to successfully treat seven patients with active CSF infection
[12]. There are no observational studies comparing the silver-impregnated VPS infection rate with either the standard or antibiotic-impregnated VPS. However, in a RCT of EVDs in children and adults, silver-impregnated EVDs have been shown to reduce infection from 21.4% (30/140) to 12.3% (17/138) (*P* = 0.042)
[13]. Two further observational studies comparing standard to silver-impregnated EVDs have also shown a reduction in infection rates
[14,15]. The commentary accompanying the EVD study acknowledges the need for a RCT to study the relative benefits of silver-impregnated catheters.

Data from the UK shunt registry (to which most neurosurgical units contribute) show that 15% of shunt revisions are for infection
[16]. In the largest randomised controlled shunt trial worldwide, the infection rate was 8.4% for primary VPS
[17]. The commonest pathogens detected are *Staphylococcus* species, but in a proportion of patients with suspected infection the organism is never determined, especially if they have already received antimicrobial treatment or the organism is very slow growing, hampering microbiologically directed treatment selection. However newer molecular approaches are increasing the diagnostic rate for a range of central nervous system (CNS) infections. Whilst a systematic review
[9] suggests that antibiotic-impregnated shunts may be an effective way of reducing the incidence of shunt infections, there is some evidence that antibiotic-impregnated VPS that become infected may be more difficult to treat leading to prolonged hospital stays
[18]. Antibiotic-impregnated VPS prevent the sensitive organisms causing infection and may allow the rifampicin-resistant organisms to survive. Subsequently this may contribute to VPS failure secondary to infection. A second follow-up report of 500 antibiotic-impregnated primary and revision VPS insertions showed sensitive organisms may still cause infection but presentation was significantly delayed compared to standard historical controls
[19]. It is plausible to suggest that antibiotic-impregnated VPS may lead to a delay in presentation allowing increased time for biofilm development on the ventricular surface rather than just the VPS. This could result in more difficult to treat, serious infection through rifampicin resistance, and warrants further investigation.

There are no economic evaluations of VPS, however four retrospective cost studies from the USA
[20-23], which include both adults and children, suggest that cost savings may be possible through reduction of infection with antibiotic-impregnated shunts. Approximately 70% of shunt operations in the UK are with antibiotic-impregnated shunts (which cost £359) and there is likely to be a significant uptake of silver-impregnated (£365) shunts by neurosurgeons despite the lack of evidence of clinical benefit. Both VPS catheters cost more than standard (£137). The potential beneficial effect on health status of these impregnated catheters is reduced shunt infection and its negative sequelae. This must be balanced against the possibility of selecting out resistant organisms or rendering infections more difficult to treat with adverse impact on outcome and increased cost for impregnated VPS. The British antibiotic and silver impregnated catheters for ventriculoperitoneal shunts multi-centre randomised controlled trial (the BASICS trial) was therefore funded to determine whether these impregnated VPS reduce early infection, compared with standard VPS, and whether this is cost-effective.

### Primary objective

To determine whether antibiotic or silver-impregnated VPS reduce infection compared to standard VPS following insertion of the first *de novo* VPS.

### Secondary objectives

• To determine the proportion of first VPS infections occurring >6 months after insertion of *de novo* VPS.

• To determine whether antibiotic or silver-impregnated VPS reduce shunt failure of any cause compared to standard VPS following insertion of *de novo* VPS.

• To assess whether the reason for shunt failure is different across the three different types of VPS.

• To determine which organisms and their resistance/sensitivities subsequently infect these three alternative VPS.

• To determine whether antibiotic or silver-impregnated VPS reduce infection following the first (non-infected) clean VPS revision for mechanical failure compared to standard VPS.

• To assess the impact of VPS infection on the patient in terms of quality of life.

• To assess the cost-effectiveness of antibiotic-impregnated and silver-impregnated VPS compared to standard VPS.

## Methods/design

### Design overview

The BASICS trial is a national three-arm, multi-centre, phase III RCT comparing antibiotic-impregnated, silver-impregnated, and standard VPS in patients with hydrocephalus undergoing insertion of their first permanent shunt. The design of the trial is presented in Figure 
1.

**Figure 1 F1:**
[figure not shown]
Flow diagram for trial.

### Research setting

The trial will be conducted across 17 paediatric and adult regional neurosurgery units in the UK and Ireland. A feasibility survey completed by 14 centres provided information on the number of eligible hydrocephalus patients and confirmed that the sample size is achievable.

### Study population

The trial will be open to all patients (children and adults) with hydrocephalus requiring treatment with a first permanent VPS who meet the eligibility criteria.

### Inclusion criteria

• Hydrocephalus of any aetiology (including idiopathic intracranial hypertension) requiring first VPS.

• Failed primary endoscopic third ventriculostomy allowed.

• Previous indwelling EVD allowed.

• Previous indwelling ventricular access device (for example Ommaya or Rickham reservoir or similar) allowed.

### Exclusion criteria

• Evidence of CSF infection prior to surgery for first VPS.

• Previous indwelling VPS.

• Active and on-going CSF or peritoneal infection.

• Multiloculated hydrocephalus requiring multiple VPS or neuroendoscopy.

• Ventriculoatrial or ventriculopleural shunt planned.

• Allergy to antibiotics associated with the antibiotic shunt.

### Primary outcome measure

Time to VPS infection following insertion of first *de novo* VPS for hydrocephalus.

### Secondary outcomes

• Time to shunt failure of any cause.

• Reason for shunt failure (infection, mechanical failure, patient failure, or other).

• Types of bacterial shunt infection (organism type and antibiotic resistance).

• Time to shunt infection following first clean revision.

• Quality of life.

• Incremental cost per shunt failure averted.

• Incremental cost per quality-adjusted life-year (QALY) gained.

### Randomisation

Patients will be randomised to standard, antibiotic, or silver-impregnated VPS in a ratio of 1:1:1. These are all CE marked medical devices used in accordance with the manufacturer’s instructions for their intended purpose. Written informed consent and assent, where appropriate, will be obtained pre-operatively, but randomisation will not occur until the trial participant is in the theatre suite so that only patients demonstrating continuing eligibility will be randomised at this stage, avoiding the randomisation of ineligible patients as far as is practically possible. Theatre staff cannot be blinded to the type of shunt inserted, but once the shunt is in position there will be no visible indications of the shunt type used. The type of shunt inserted will not be disclosed outside the operating theatre. Training on non-disclosure of shunt type will be provided to all staff members present at surgery. The majority of shunt revisions and removals for infection happen as emergencies and are managed by the on-call team. The likelihood of the same surgeon who inserted the shunt being involved in the decision to remove the shunt is low given the work rotas of surgical staff. However, this will be tracked by logging the staff involved in surgery and in the decision to remove the shunt. This process is the same as that successfully implemented for the catheter infections in children (CATCH) trial (ISRCTN34884569) and will form part of the trial monitoring report presented to the trial management group.

### Proposed sample size

Approximately 30% of new VPS will fail within the first 6 months of insertion due to shunt complications, which will include infection but also malfunction and mechanical failure, typically secondary to catheter or valve obstruction and peritoneal complications. When a VPS has failed for reasons other than infection then this prevents infection being observed. Infection is the event of interest with all other reasons for shunt failure being competing risks. The trial will compare antibiotic-impregnated versus standard VPS, and silver-impregnated versus standard VPS. A Bonferroni adjustment has been made to allow for the multiple comparisons and a statistical significance level of 0.025 will be used accordingly. The sample size calculation is based on Pintilie
[24] assuming time to any type of event (of interest or competing risks) follows an exponential distribution. Using a 2-year accrual period with 6-month follow-up, once accrual has been completed and a competing risks event rate of 30% across trial arms with the event rate of interest (infection) being 8% in the standard arm and 4% in the treated arms (hazard ratio of 0.49), then with 5% loss to follow-up we would require 989 patients to provide 80% power. The power varies according to changes in the event rate with a fixed total sample size of approximately 1,143. Allowing for 5% loss to follow-up a sample size of 1,200 participants allows a hazard ratio of 0.49 to be detected over a range of baseline event rates (0.05 to 0.1) with good statistical power. The value of 8% is supported elsewhere
[17], in addition, infection rate surveillance over 10 years (1993 to 2003) at Great Ormond Street Hospital, London, UK, involving over 1,500 insertions has demonstrated that while there are fluctuations in monthly infection rates that overall the rate has remained remarkably stable around this level. Observed fluctuations in infection rates within a centre will be influenced by the size of the denominator. Reduction of infection is a priority and therefore it could be argued that much smaller differences than those the study is powered to detect are still important. However the investigators believe that a strong effect is required to inform clinical practice and establish a first-line treatment policy across the National Health Service (NHS). This is in part due to the large differences in cost between the VPS; we need to warrant expenditure on the type of VPS as opposed to other infection control activities.

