### Statistical analysis

The primary analysis will be by intention-to-treat principle as far as is practically possible and a full statistical analysis plan will be developed prior to comparative analysis. Results will be presented throughout using 97.5% confidence intervals and a 2.5% level of statistical significance. Analysis of the primary outcome will be by cumulative incidence. The Fine and Gray
[25] regression method will be used to directly model the cumulative incidence function. In addition two semi-parametric models described in Scheike and Zhang
[26] will be used to consider time-varying effects. Time-to-event outcomes where competing risks is not an issue will be analysed using Kaplan–Meir curves, log-rank tests, and Cox proportional hazard models. Assumptions of proportional hazards will be investigated. Categorical outcomes will be analysed using Chi-squared test. An interim analysis will be conducted halfway through the trial after approximately 50% of the total events have been observed using Haybittle
[27].

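### Cheap improvement, not an error: Holm's step-down would keep the 5% family-wise error and add about 3.5 to 4 points of power per comparison at 1,200 patients, if both catheters work

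*Protocol article*

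**What the plan says.** The sample size section of the protocol article defines a family of two comparisons with a shared control: "The trial will compare antibiotic-impregnated versus standard VPS, and silver-impregnated versus standard VPS". It then sets the level for each: "A Bonferroni adjustment has been made to allow for the multiple comparisons and a statistical significance level of 0.025 will be used accordingly". The statistical analysis section carries this over to reporting: "Results will be presented throughout using 97.5% confidence intervals and a 2.5% level of statistical significance". Allocation is equal across the three arms. The trial is sized on the same benefit for both impregnated catheters, with the infection rate "being 8% in the standard arm and 4% in the treated arms (hazard ratio of 0.49"). Under those assumptions, "with 5% loss to follow-up we would require 989 patients to provide 80% power". The planned total is 1,200, about 1,143 before the allowance for loss, so that power holds up over baseline infection rates from 0.05 to 0.1. No step-down procedure is mentioned.

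**The concern.** Single-step Bonferroni holds each comparison to 0.025 whatever the other one shows. Holm tests the smaller P value at 0.025 and, only if that succeeds, the other at 0.05. It bounds the family-wise error at 5% under any dependence between the tests, and it cannot reject less than Bonferroni.

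The two rules differ in one situation: one catheter has met 0.025 and the other has a P value between 0.025 and 0.05. The protocol would call the second catheter unproven, although a 5% family-wise error allows the claim. Each catheter is a separate purchasing question for the health service, so the second verdict matters. A plan sized on equal benefit in both impregnated arms is also the case in which a step-down rule gains most.

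**Working it through.** **Inputs (sample size and randomisation sections).** Two comparisons at 0.025; 6-month infection 8% v 4%; 30% competing events in every arm; 2 years' accrual plus 6 months; 5% loss; 1:1:1 allocation; 989 patients for 80% power; about 1,143 patients before loss, 1,200 planned.

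**Step 1: reproduce 989.**
- With exponential times, the standard arm has a total hazard of −ln(1 − 0.38)/0.5 = 0.956 per year, of which infection is 0.08/0.38, or 0.2013. A treated arm has −ln(1 − 0.34)/0.5 = 0.831, of which infection is 0.04/0.34, or 0.0978. The hazard ratio is 0.0978/0.2013 = 0.486 (stated as 0.49).
- The probability of an observed infection is (λ_inf/λ) × [1 − (e^(−0.5λ) − e^(−2.5λ))/(2λ)], which gives 0.1524 (standard) and 0.0798 (treated).
- Events per comparison: (2.2414 + 0.8416)² / (0.25 × ln(0.4857)²) = 9.505/0.1304 = 72.9.
- Patients per arm: 72.9/(0.1524 + 0.0798) = 314.1. Three arms: 942.3. Times 1.05: **989.4**, which matches the protocol.
- The article does not state sidedness. One-sided 0.025 gives only 817, so the design is two-sided.

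**Step 2: Holm at the design point.** Take the two test statistics as jointly normal, each with mean 2.2414 + 0.8416 = 3.083. The shared standard arm gives correlation 0.5 under the null. Under the alternative the event counts are unequal and it is about (1/0.1524)/(1/0.1524 + 1/0.0798) = 0.34. With correlation 0.5:
- B = P(both exceed 2.2414) = 0.6872.
- X = P(one exceeds 1.960 and the other exceeds 2.2414) = 0.7328.
- Per comparison: Bonferroni 0.800; Holm 0.800 + (X − B) = 0.846. Gain **4.6 points**.
- Both: Bonferroni B = 0.687; Holm 2X − B = 0.778. Gain **9.1 points**.
- At least one: 0.800 + 0.800 − 0.687 = 0.913 under either rule, because Holm's first step is the Bonferroni test.

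A simulation of 4 million trials agrees. With correlation 0.34 the gains are 4.9 and 9.8 points.

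**Step 3: the planned size.** 1,143/3 = 381 per arm, so events per comparison are 381 × (0.1524 + 0.0798) = 88.4. The mean of the statistic is (√88.4/2) × |ln HR|, which is 3.396 for HR 0.486 and 3.354 for HR 0.49. Bonferroni power is then 87.6% or 86.7%.

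| 1,143 patients, 8% baseline | Per comparison | Both |
|---|---|---|
| HR 0.486, correlation 0.5 | 87.6% → 91.1% | 79.6% → 86.6% |
| HR 0.486, correlation 0.34 | 87.6% → 91.4% | 78.5% → 86.0% |
| HR 0.49, correlation 0.5 | 86.7% → 90.4% | 78.3% → 85.6% |
| HR 0.49, correlation 0.34 | 86.7% → 90.6% | 77.1% → 85.0% |

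The gains are **3.5 to 3.9 points** per comparison and **7.0 to 7.9 points** for both. Over the protocol's range of baseline rates, with infection halved, they run from 5.4–5.7 and 10.8–11.4 points at 5% down to 2.1–2.6 and 4.2–5.1 points at 10%.

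**Step 4: only one catheter works (correlation 0.5, simulated).** Power for the effective catheter goes from 80.0% to 80.2%. The chance that the ineffective one is declared effective rises from 2.5% to 4.2% at the 989-patient design point and to 4.4% at the planned size.

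**Step 5: neither works.** The family-wise error is 4.6% under both rules at correlation 0.5.

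**The case against.** The strongest reply is that nothing here is wrong. Bonferroni controls the error; the level, the power and 989 agree with each other; and the 97.5% intervals match the tests and have simple joint coverage, which Holm does not offer. All of this stands, and it is why the point is an improvement and not a correction.

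The gain is also conditional. Equal benefit is a sizing assumption, and the background section reports no observational comparison of silver shunts with the other types. If one catheter fails, Holm buys almost nothing and gives the ineffective one a better chance of a false claim. That stands too, although the error stays within the 5% family-wise limit.

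The protocol also says that a strong effect is needed to change practice. That remark concerns the effect size for which the trial is powered. A stricter significance level is not a minimum-effect rule, so the remark does not justify Bonferroni over Holm.

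A reader might infer that the protocol gives away about 5 and 9 points of power as it stands. The documents do not support this. Those figures belong to 989 patients, the trial plans 1,200, and both catheters must work.

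**Conclusion.** The fixed 0.025 rule is valid and consistent with the rest of the plan. It can be improved at no cost in patients. At 1,200 patients and 8% baseline, Holm would add about 3.5 to 4 points per comparison and 7 to 8 points for showing both, provided that both hazard ratios are near 0.49. With one effective catheter the gain is about 0.2 points, and the chance of at least one success is the same in every case.

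These figures assume jointly normal statistics, correlation between 0.34 and 0.5, equal effects in the impregnated arms and two-sided tests, and they ignore the interim look. It should not be inferred that the trial is underpowered, that its error control fails, or that the sample size must change.

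**What to change.** For the primary outcome only, replace the fixed level with a rule such as: *The smaller of the two P values is tested at 0.025; if it is significant, the other is tested at 0.05; otherwise neither comparison is declared significant.* Keep 97.5% intervals for both comparisons, and show a 95% interval as well for the one tested second. Leave the sample size as it is.

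The change must be prespecified before unblinding. The analysis plan, which the article says will be developed before comparative analysis, is the natural place.

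Costs:
- The second comparison's 97.5% interval may disagree with its test, and the displayed pair no longer gives simple simultaneous coverage.
- An ineffective catheter's false-positive chance rises from 2.5% to about 4.2–4.4% when the other works.
- The primary outcome follows a different rule from the 2.5% level used elsewhere, so the sentence applying that level throughout needs an exception.
- The plan must state how the second comparison is tested if the first crosses the interim boundary.

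### The 80% power for 989 patients depends on an undisclosed projection of about 15% infected in the standard arm; at the recruited size, power runs from about 57% to 88% depending on how infections continue after month 6

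*Protocol article*

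**What the plan says.** All design inputs are in the article's section on the proposed sample size. Event times are modelled by "assuming time to any type of event (of interest or competing risks) follows an exponential distribution". Accrual lasts 2 years, with 6 months of follow-up after it closes. The competing event rate is 30% in every arm. Infection is 8% in the standard arm and 4% in each impregnated arm, with a hazard ratio of 0.49. For the two comparisons with standard, "a statistical significance level of 0.025 will be used accordingly". The result is stated as "then with 5% loss to follow-up we would require 989 patients to provide 80% power".

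The section then fixes the total at about 1,143, or 1,200 after 5% loss. It says this gives good power for a hazard ratio of 0.49 over baseline infection rates from 0.05 to 0.1.

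The section opens by tying a failure proportion of about 30% to the first 6 months. No window is attached to the 8% and 4%. The support for 8% is:
- the abstract: "failures caused by infection occur in approximately 8% of primary cases";
- the Background, on the largest shunt trial: "the infection rate was 8.4% for primary VPS";
- the sample-size section: ten-year surveillance at one hospital, with an overall rate around this level.

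**The concern.** In a time-to-event design, power comes from the number of infections, so it matters when 8% is reached and what happens afterwards. Patients are followed for 6 to 30 months. If 8% is a 6-month figure and the exponential model runs on, the calculation counts almost twice that proportion as infected. If 8% is closer to the whole infection burden of a first shunt, far fewer infections will be seen than the design counts on. The article does not say which is meant, and a reader who sees 8% v 4% will not realise that the power rests on about 15% v 8%.

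The stakes are in how a null result is read. The investigators want a strong effect that can set first-line policy across the health service. A comparison reported as having at least 80% power, when the true figure may be well below that, could be taken as good evidence against a device that works.

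**Working it through.** **Inputs.** From the sample-size section: significance level 0.025 per comparison (taken as two-sided; sidedness is not stated), power 80%, infection 8% v 4%, competing events 30%, accrual 2 years, further follow-up 0.5 years, loss 5%. From the randomisation section: 1:1:1, so each comparison uses two thirds of the patients. Assumption under test: 8%, 4% and 30% are cumulative incidences at 0.5 years.

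**Step 1: hazards.** Total hazard L = -ln(1 - p_inf - p_comp)/0.5, and infection hazard = L × p_inf/(p_inf + p_comp).
- Standard: L = -ln(0.62)/0.5 = 0.956 per year; infection 0.2013.
- Impregnated: L = -ln(0.66)/0.5 = 0.831 per year; infection 0.0978.
- Ratio 0.0978/0.2013 = 0.486, close to the stated 0.49.

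**Step 2: infections needed.** 4 × (2.2414 + 0.8416)²/ln(HR)² = 72.9 per comparison at HR 0.486, and 74.7 at HR 0.49.

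**Step 3: probability of an observed infection.** (infection hazard/L) × {1 - [exp(-0.5L) - exp(-2.5L)]/(2L)}.
- Standard: (0.2013/0.956) × {1 - (0.620 - 0.0916)/1.912} = 15.24%.
- Impregnated: (0.0978/0.831) × {1 - (0.660 - 0.1252)/1.662} = 7.98%.
- Mean 11.61%.

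**Step 4: sample size.** Two arms: 72.9/0.1161 = 628. Three arms: 1.5 × 628 = 942. Allowing for loss: 942.3 × 1.05 = **989**, as stated. The factor 1.05 also fits the article's other pair: 1,143 × 1.05 = 1,200.

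**Other readings.** Rates reached at 12 months or later need 1,432 or more. Six months of follow-up for everyone needs 1,914 or more. A simple comparison of 8% v 4% needs 2,007 before loss. Every variant within 3% of 989 uses 6-month rates continued at constant hazard. The section describes the 30% first as all failures including infection and then as the competing rate; the first of these gives 908 to 1,050 and still implies 15% to 17% infected in the standard arm.

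**What the reproducing model projects.** Of the standard-arm infections, (15.24 - 8)/15.24, just under half, fall after month 6. Standard shunts failed for any reason: 1 - exp(-0.956) = 62% by 12 months and 1 - exp(-0.956 × 2.5) = 91% by 30 months.

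**Power at 1,143 evaluable** (381 per arm, 762 per comparison). Power = Φ(√(d/4) × |ln HR| - 2.2414), where d = 381 × (sum of the two infection proportions). After month 6, the late infections added are S × (h/H) × {1 - [1 - exp(-2H)]/(2H)}, where S = 0.62 or 0.66 and h and H are the reduced infection and total hazards. The ranges run from HR 0.49 to HR 0.486. The reductions are illustrative assumptions, not figures from the article.

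| After month 6 | Infected, standard v impregnated | Infections d | Power |
|---|---|---|---|
| Hazards constant | 15.2% v 8.0% | 88 | 87-88% |
| All hazards halve | 12.7% v 6.5% | 73 | 79-80% |
| Only infection hazard halves | 11.8% v 6.0% | 68 | 76-77% |
| All hazards fall to a quarter | 10.7% v 5.4% | 61 | 71-72% |
| Only infection hazard falls to a quarter | 10.0% v 5.0% | 57 | 67-69% |
| 8%/4% is the trial total | 8% v 4% | 46 | 57-58% |

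**Range of baseline rates at 1,143, HR 0.49.** At baseline 0.05, constant hazards give 9.9% v 5.1% infected, 57 infections and 67% power. If 0.05 v 0.025 is the total, d = 381 × 0.075 = 28.6 and power is 37%. At baseline 0.10 the figures are 93% and 68%.

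**The case against.** The strongest reply is that nothing has been miscalculated. The exponential assumption and the follow-up schedule are declared, the section opens with a 6-month failure proportion, so reading all the rates as 6-month rates is natural, and 989 follows exactly. That stands: this is not an arithmetic error, though a reader who meets 15% where the article says 8% might infer one.

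Nor does any passage show that 8% is the total over follow-up. The periods behind the abstract's figure, the 8.4% and the surveillance data are not given. The primary outcome has no 6-month limit, so later infections count. A secondary objective asks what share of first infections occur after 6 months, and the Background cites delayed presentation with antibiotic-impregnated shunts. The Background's wish to "determine whether these impregnated VPS reduce early infection" is description and does not restrict the endpoint. The Background also quotes infection rates of 3% to 27%, so 15% is not implausible in itself. All of this stands, and it makes 57-58% a lower bound.

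The margin from 989 to 1,200 also counts: it absorbs a halving of all late hazards. A reader might infer that the design has about 50% power. That figure belongs to 989 patients with 8%/4% as the total, and the trial recruits 1,200.

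A reader might also infer that the interim analysis, set at about half of total events, would slip to near the end of the trial. That requires holding the total at the 119 infections projected under constant hazards (381 × [15.24% + 2 × 7.98%]), and the article states no such total.

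What the reply does not remove is the missing window, the undisclosed projections, and the fact that 91% of standard shunts failing by month 30 has no support in the article.

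**Conclusion.** The point holds as one of disclosure and robustness. The stated 80% is right under one reading only, and that reading needs nearly twice the quoted infection proportion to be observed. With about 1,143 evaluable, power is 57% to 88%. It stays near 80% if all hazards fall by no more than about half after month 6, and is below that if infections are more concentrated early. The claim of good power over baseline rates 0.05 to 0.1 fails at its low end on any reading: 67% with constant hazards, 37% if 0.05 is the total.

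These figures rest on a two-sided 0.025 level, a hazard ratio of 0.486 to 0.49, uniform accrual over 2 years, and illustrative late-hazard reductions. Where the truth lies depends on the period over which the cited 8% was observed, which the article does not give.

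**What to change.** In the sample-size section:
- State the time window of the 8%, 4% and 30%.
- Say that the model projects about 15.2% v 8.0% infected by the end of the study, and that about 73 to 75 infections are needed per comparison.
- Replace the single 80% figure and the claim of good power with power at about 1,143 evaluable under constant, declining and zero infection hazard after month 6, and across baseline rates 0.05 to 0.1.

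This is a rewording and needs no extra patients. The cost is a less favourable stated power.
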